#### Face recognition

Face recognition is a subtest from the Rivermead Behavioral Memory Test (RBMT) [87] and measures visual, nonverbal long term memory. Two versions (C+D) are combined to prevent a ceiling effect. In this test the participant is shown 10 cards with faces one at a time for 5 seconds. After a short interval of approximately 2 minutes, the participant is shown 20 cards, including 10 shown before and 10 cards with new faces. The participant has to recognise whether the card was shown before or not. The outcome measure is the number of faces correctly recognized minus the number of faces incorrectly recognized. The worst score is -20 and the best score is +20.

#### Picture recognition

Picture recognition is also a subtest from the RBMT [87], which measures visual, verbal long term memory. Two versions (C+D) are combined to prevent a ceiling effect. The participant is shown each of the 20 cards with drawings of objects for 5 seconds. With each card, the participant is requested to name the object on the card. After a short interval of approximately 2 minutes, the participant is shown 40 cards, including 20 shown before and 20 cards with new objects. The participant has to recognise whether the card was shown before or not. The outcome measure is the number of objects correctly recognized minus the objects that were incorrectly recognized. The lowest score is -40 and the maximal score is +40.

#### Category fluency test

The category fluency test is a verbal fluency test which can be used to evaluate EF [88,89]. The participant is asked to name as many examples of a given category as possible, within 1 minute. This requires a strategic search mechanism to retrieve information from semantic memory [90]. This study uses the category 'animals' and 'professions' [91]. The outcome measure is the total number of animals and professions produced.

#### Visual memory span (forward and backward)

The visual memory span is a subtest of the WMS-R [84]. The visual memory span stimuli consist of squares printed on a two dimensional card and requires the participant to repeat a number of tapping sequences that becomes longer with each trial. The visual memory span contains a forward and a backward sequence, similar to the digit span test. It was initially added to the WMS-R as a visual analogue digit span test. The forward condition is used as a measurement of attention and immediate visual memory, the backward condition is used as a measure of attention and visual working memory [84]. Scores range from 0 (worst) to 14 (best) in the forward condition and from 0 (worst) to 12 (best) in the backward condition.

#### Picture completion

Picture completion is a subtest from the Groninger Intelligence Test (GIT) [92]. The GIT is a test of general intelligence that is used in the Netherlands for purposes comparable to the Wechsler Adult Intelligence Scale (WAIS). The picture completion subtest measures visual perception, specifically, alertness to visual detail [93]. Available literature suggests that this subtest may have utility as a measure of suboptimal effort, especially in less-educated participants and is a moderately effective measure of response bias [93]. Figures are not completely drawn and participants are instructed to describe the missing parts of pictured objects. The figures increase in difficulty. After 20 figures or after 5 false descriptions in a row, the subtest is finished. The best score is 20, representing 1 point for every correct description.

#### Stroop task

The version of the Stroop task that is commonly used in the Netherlands [94] consists of three subtasks which the participant performs as quickly as possible; each test has a 45 second time limit. In the first subtask, participants are presented with four color words, i.e. red, green, blue and yellow, printed in black ink in ten rows with ten names each. The participant's task is to read as many color names in the right order. Second, the participant is presented with a similar paper, but this time with solid color patches (red, green, blue and yellow) that have to be named in the right order. In the final subtask the names of the colors are written in a different color ink than the meaning of the word (i.e. the word 'blue' written in red ink) and the participants again need to name the color of the ink, thus suppressing reading the word, which is a highly automatic reaction. This test has been found to correlate moderately well with other tests of response inhibition [95], which is an EF task [96]. The score on each card is the total correct mentioned colors within 45 seconds. The final score is the score on card 2 minus the score on card 3. A lower final score indicates a better performance of inhibition.

#### Digit symbol substitution test (DSST)

The DSST is a subtest of the WAIS-Revised [84] and has been widely used as a measure of general information processing speed in studies of cognitive aging [97]. Test scores correlate with general intelligence, cognitive impairment, chronological age and activation in the frontal regions [98-101]. Participants are presented with a rectangular grid of numbers. For each of these numbers, participants are instructed to substitute the appropriate symbol according to a code that appears at the top of the page. The DSST score is recorded as the number of correct symbols drawn in 2 minutes.

### Assessment of depression level and anxiety

The level of depression and anxiety will be assessed by the following questionnaires:

#### Geriatric depression scale (GDS)

The Dutch version [102] of the GDS is a 30-item questionnaire used to measure general mood [103]. The GDS is a reliable and valid self-rating depression screening scale for elderly populations [104]. The GDS questions are answered by 'yes' or 'no' depending on which response is most appropriate at the time of measurement, with 0 or 1 point for each answer. Higher scores indicate a higher level of depression.

#### Symptoms checklist 90 (SCL-90)

Two subscales from the Dutch version [105] of the SCL-90, a 90-item self-report symptom inventory designed to reflect patterns of current psychological symptoms, will be used to measure depression and anxiety [106,107]. The depression and anxiety subscale includes 15 and 10 items respectively. Each item is rated on a 5-point likert scale, from 1 (not at all) to 5 (extremely). A higher score indicates more symptoms of depression or anxiety.

### Assessment of rest-activity rhythm

Rest-activity data are collected by the use of an Actiwatch activity monitor (Cambridge Neurotechnology Ltd., Cambridge, Great Britain). Actiwatches are small activity monitors worn on the dominant wrist for several days. Three variables below are analysed.

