### Intervention

The intervention consist of a daily 30 minute walk, 5 times a week under supervision of an assistant, e.g. medical staff, volunteers or family members. Depending on the participant, the assistant, the living area and the weather, the intervention can take place in the morning or afternoon, inside or outside, during midweek and/or weekends. Each day the participant has walked will be carefully noted, together with the time of day, duration and whether it was inside or outside.

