### Procedure

The outcome variables are measured at baseline (pre-treatment: T0), after 6 weeks of intervention (post-treatment: T1) and after 3 (T2), 6 (T3), 9 (T4), 12 (T5) and 18 (T6) months of intervention. Trained experimenters, blinded to the intervention assignment, will administer the neuropsychological tests, physical tests and level of depression, anxiety and pain. The nursing staff fills in questionnaires to measure QoL, ADL and define the stage of dementia. The other variables are objective measurements.

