#### Relative amplitude (RA)

The RA measures the relative difference in the 10 most active consecutive hours (M10) and the uninterrupted least active 5 hours period (L5) within a 24 hours cycle. RA is calculated as the difference between the means of M10 and L5 in the average 24 hours pattern [108]. Because it is a relative measure, variance resulting from differences in sensitivity of actigraphs is reduced. Higher values indicate a larger difference between daytime activity and night time rest and therefore a better rhythm.

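### Relative amplitude is recorded while the supervised walks continue, so the walk itself can raise it without any change in night rest or other activity

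*Protocol article*

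**What the plan says.** **Timing.** The Procedure section of the protocol article places the first follow-up "after 6 weeks of intervention (post-treatment: T1") and the others "after 3 (T2), 6 (T3), 9 (T4), 12 (T5) and 18 (T6) months of intervention". T1 carries a post-treatment label, but the same sentence counts it and all later visits as time on the intervention. No visit is planned after the walks have ended.

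**Intervention and control.** Under Intervention: "The intervention consist of a daily 30 minute walk, 5 times a week under supervision of an assistant". The hour is not fixed, since "the intervention can take place in the morning or afternoon, inside or outside, during midweek and/or weekends". Under Study design and randomization, the control group meets three times a week for tea or another sedentary activity.

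**Measurement.** Under Assessment of rest-activity rhythm: "Actiwatches are small activity monitors worn on the dominant wrist for several days", and "Three variables below are analysed". These are interdaily stability (IS), intradaily variability (IV) and RA. RA is the mean of M10 minus the mean of L5 in the average 24-hour pattern, and it is interpreted thus: "Higher values indicate a larger difference between daytime activity and night time rest and therefore a better rhythm". L5 appears only as a component of RA.

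**Walk log.** Under Intervention: "Each day the participant has walked will be carefully noted, together with the time of day, duration and whether it was inside or outside". Neither the actigraphy section nor Statistical analysis uses this log when the rhythm variables are computed.

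**The concern.** The treatment is a bout of daytime activity, and the outcome is computed from recorded activity over the same days. One arm has the bout in its recordings and the other has a sedentary session instead. RA rises when daytime activity is added, and the protocol article reads any rise as a better rhythm.

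The Background motivates this outcome by sleep disorders, night-time wakefulness, daytime sleeping and long hours in bed or sitting. A reader of the results will want to know whether regular walking changes the night, or the activity people take up unprompted. RA as planned cannot separate such a change from the walk being recorded. Because all six follow-ups (T1 to T6) are affected, the walk's contribution would appear as a lasting difference between the groups in the planned repeated-measures analysis, and could be reported as an improved rhythm.

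**Working it through.** The documents give no figure for actigraphy, so there is none to reproduce. The check is whether the stated definitions produce a group difference when nothing changes except the walk.

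**Step 1: do the recordings contain walks?** Five walks a week leave 7 − 5 = 2 walk-free days. Three or more recorded days within one week therefore include at least one walk day if all five walks are delivered. The article does not remove walk days or walk minutes.

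**Step 2: RA.** Let A be the net extra count in the hour that holds the walk, that is, walk activity minus what the person would otherwise have done. A morning or afternoon walk lies within the 10 most active hours and outside the 5 least active. Averaged over the recording it adds A × (walk days / recorded days) to the sum over the M10 window. This holds whether the hour is fixed or varies inside that window. Dividing by 10 hours:

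Rise in RA = A × (walk days / recorded days) / 10, with L5 unchanged.

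A is not in the documents. The assumed range is 50 to 300 counts per walk hour.

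| A | 5 of 7 days | 5 of 5 days |
|---|---|---|
| 50 | 50 × (5/7)/10 = 3.6 | 5.0 |
| 150 | 150 × (5/7)/10 = 10.7 | 15.0 |
| 300 | 300 × (5/7)/10 = 21.4 | 30.0 |

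Example with assumed M10 = 110 and L5 = 30: RA is 80. With A = 150 on 5 of 7 days it becomes 90.7, a rise of 10.7/80 = 13%. If RA is instead normalised as (M10 − L5)/(M10 + L5), it goes from 80/140 = 0.571 to 90.7/150.7 = 0.602. The conclusion is the same for either form.

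**Step 3: all three variables by simulation.** Hourly data were simulated with and without a daytime walk, the night left untouched. There were 36 scenarios: three activity profiles, 5 or 7 recorded days with 5 walks, A of 50, 150 or 300, and a fixed or varying walk hour. Assumed levels were 100 to 150 counts per hour by day and 20 to 50 by night.

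| Variable | Better if | Change when only the walk is added |
|---|---|---|
| RA (M10 − L5) | higher | up in all 36: about +3 to +30 on a base of 60 to 138 |
| RA, normalised | higher | up in all 36: +0.004 to +0.098 on a base of 0.40 to 0.79 |
| IS, fixed walk hour | higher | +0.01 to +0.33 |
| IS, varying walk hour | higher | −0.05 to +0.04 |
| IV | lower | −0.04 to +0.18 |
| L5 | – | 0.00 |

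IS behaves this way because a walk at the same hour sharpens the average 24-hour pattern, while a walk at changing hours mainly adds day-to-day variance. For IV, a single active hour raises both the hour-to-hour differences and the overall variance, so the ratio can go either way.

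**Step 4: can the size be put in standard deviations?** Not reliably. If the walk is taken as 3 to 8 times the usual daytime level, one set of assumed profiles gives an RA shift of about 0.24 to 0.76 between-person SD and another gives 0.15 to 0.54. At 1.5 to 2 times the daytime level, the second set gives only 0.03 to 0.08 SD.

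**The case against.** **More daytime activity is part of the target.** The Background names daytime sedentariness as a contributor to disturbed rhythm, and the Discussion presents walking as something that could become routine care. The rhythm actually lived while walking is then a legitimate quantity, and the article calls the outcome rest-activity rhythm, not sleep. This stands. It is the reason to keep the planned variables unmasked. It does not justify reading a higher RA as a change in the night or in unprompted activity.

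**The effect may be small.** The monitor is on the wrist, walking aids are allowed and attendance may be incomplete, all of which may lower A. This also stands, and the size cannot be stated from the documents.

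**The article is condensed.** Rules on recording days and sensitivity analyses may sit in the full protocol or analysis plan. This stands for those details. The visit times, the three variables, the RA formula and its interpretation are fixed in the article, and the problem follows from them together.

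**Stronger readings to avoid.** A reader might infer that all three variables are inflated in favour of walking. They are not: a steady gain in IS needs a fairly constant walk hour, which the Intervention section does not require, and IV can worsen. A reader might also infer that a positive result would show only that the walks took place. That does not follow, because RA also reflects L5 and all other daytime activity, so a difference could include real change.

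**Conclusion.** The point holds for RA. Given measurement during the intervention, a sedentary control condition and RA scored as M10 minus L5, the walk alone tends to raise RA in the walking group with the night unchanged. This assumes that the walk is recorded as more activity than it displaces (A above zero), that it falls within the 10 most active hours, and that people do not compensate by being less active at other times.

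For IS, the direction is upward if the walk hour is fairly constant and undetermined if it varies. For IV it is undetermined. The size is unknown for all three. The illustrative RA rise of about 3.6 to 30 counts depends on assumed counts and full attendance.

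Rest-activity rhythm is one of eight outcome areas in the Abstract, so this does not threaten the trial as a whole. It limits what a higher RA can be taken to mean.

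**What to change.** 1. Keep IS, IV and RA as planned, and describe them as measures of the total on-treatment rhythm.
2. Report L5 (night activity) and M10 separately by group. A daytime walk does not enter L5 directly.
3. Add a sensitivity analysis that recomputes IS, IV and RA with the logged walk minutes masked, and masks a matching clock window in controls. Specify the rule for that window in advance, because walk times can differ between participants in one residence. Masking is preferable to substituting values from walk-free days, of which there are about two a week and perhaps none in a short recording.
4. State that a higher RA will not be interpreted as improved rhythm or sleep beyond the walk itself unless L5 or the masked RA supports it.

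No new outcome data are needed, provided the log holds a clock time for each walk and the monitor stores epochs shorter than an hour. The article does not give the epoch length. With hourly data only, the whole walk hour would have to be masked.

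The cost is some extra processing and a short addition to the analysis section. The sensitivity analysis loses up to 30 minutes per walk day, which is 30/1440 = 2.1% of the day and 30/600 = 5% of the M10 window. The reading of RA may become less favourable.

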#### Interdaily stability (IS)

The IS serves as a measure to which extent the activity patterns of all included 24 hour periods resemble each other. IS is calculated as the ratio between the variance of the average 24 hours pattern around the mean and the overall variance [108]. Higher values indicate a more stable rhythm between days.

#### Intradaily variability (IV)

The IV quantifies how well the continuity of an arousal state (sleep/activity) is. Normal rest-activity patterns will show every 24 hours one major active period (day) and one major resting period (night) and therefore show a low IV. IV is calculated as the ratio of the mean squares of the difference between successive hours (first derivative) and the mean squares around the grand mean (overall variance) [108]. Lower values indicate a better rest-activity pattern.

#### Relative amplitude (RA)

The RA measures the relative difference in the 10 most active consecutive hours (M10) and the uninterrupted least active 5 hours period (L5) within a 24 hours cycle. RA is calculated as the difference between the means of M10 and L5 in the average 24 hours pattern [108]. Because it is a relative measure, variance resulting from differences in sensitivity of actigraphs is reduced. Higher values indicate a larger difference between daytime activity and night time rest and therefore a better rhythm.

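### Relative amplitude is defined as a plain difference in device counts, which cannot have the relative, sensitivity-reducing property that the same paragraph gives it

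*Protocol article*

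**What the plan says.** The section Assessment of rest-activity rhythm introduces the Actiwatch outcomes with the words "Three variables below are analysed": interdaily stability (IS), intradaily variability (IV) and relative amplitude (RA).

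The RA section makes three statements:

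- What it measures: "The RA measures the relative difference in the 10 most active consecutive hours (M10) and the uninterrupted least active 5 hours period (L5").
- How it is computed: "RA is calculated as the difference between the means of M10 and L5 in the average 24 hours pattern", citing reference [108].
- What property it has: "Because it is a relative measure, variance resulting from differences in sensitivity of actigraphs is reduced".

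The second statement is the only computational definition of RA in the article, and it contains no division. The two companion sections do spell out a normalisation. For IS, "IS is calculated as the ratio between the variance of the average 24 hours pattern around the mean and the overall variance". IV is likewise given as a ratio, of the mean squared hour-to-hour change to the overall variance. Both cite the same reference [108].

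**The concern.** The difference of two mean activity levels carries the units of those levels, here device counts. Subtraction cancels an offset common to both terms. It does not cancel a multiplicative sensitivity, which is how one device reading higher than another on the same movement would normally show itself. The computing rule therefore lacks the property that the following sentence relies on.

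This is more than missing detail, because the article gives a complete rule and the rule yields a different quantity from the one named. An analyst who codes the sentence literally obtains an absolute amplitude under the label RA. Differences in sensitivity between devices would then sit inside the outcome as noise. Two participants with quite different relative rhythms could also receive the same score.

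**Working it through.** **Inputs.** The documents supply the rule (mean of M10 minus mean of L5 on the average 24-hour pattern), the claimed property (less variance from device sensitivity) and the ratio definitions of IS and IV. They state no RA value, activity count or sensitivity figure, so there is no plan figure to reproduce. All counts, gains and coefficients of variation (CVs) below are illustrative assumptions.

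**Step 1: algebra.** Let a device multiply every count by a gain g.

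- As written: gM10 - gL5 = g(M10 - L5), proportional to g.
- Normalised: (gM10 - gL5)/(gM10 + gL5) = (M10 - L5)/(M10 + L5), free of g.

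Any denominator that scales with the counts, such as the 24-hour mean, also cancels g.

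**Step 2: a simple case.** Assume M10 = 200 and L5 = 20.

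| g | M10 - L5 | (M10 - L5)/(M10 + L5) |
|---|---|---|
| 0.8 | 160 - 16 = 144 | 144/176 = 0.818 |
| 1.0 | 200 - 20 = 180 | 180/220 = 0.818 |
| 1.2 | 240 - 24 = 216 | 216/264 = 0.818 |

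The rhythm is identical in all three rows, and the written score moves by 20% in step with g.

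**Step 3: all three variables together.** On one simulated 7-day hourly series rescaled by gains from 0.8 to 1.25, the plain difference ran from 112.9 to 176.3 (141.1 at g = 1). The normalised index stayed at 0.780, the difference divided by the 24-hour mean at 1.640, IS at 0.813 and IV at 0.532. RA as written is the only rest-activity variable that responds to gain.

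**Step 4: cost in precision.** Assume M10 has mean 200 and SD 30, L5 has mean 25 and SD 5, the two are independent, and g has mean 1 and a given CV independent of both. Write D = M10 - L5. Then E(D) = 175 and Var(D) = 900 + 25 = 925, and

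Var(gD)/Var(D) = 1 + CV² × (1 + 175²/925) = 1 + 34.11 × CV².

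| CV of g | Variance ratio, plain difference | Simulated (200,000 draws) | Simulated, normalised index |
|---|---|---|---|
| 5% | 1 + 34.11 × 0.0025 = 1.085 | 1.084 | 1.00 |
| 10% | 1 + 34.11 × 0.01 = 1.341 | 1.341 | 1.00 |
| 20% | 1 + 34.11 × 0.04 = 2.364 | 2.355 | 1.00 |

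These ratios are for a single measurement per participant. How far they carry into the repeated-measures analysis depends on whether a participant keeps the same device, which the article does not say.

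**Step 5: same score, different rhythm.** M10/L5 of 200/20 and of 280/100 both give a difference of 180. Normalised, they give 180/220 = 0.818 and 180/380 = 0.474.

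**The case against.** The strongest reply is that the denominator was dropped in condensing the text. The variable's name, the description of what it measures and the rationale all say relative; only one sentence is short, and it cites the same source as IS and IV. That is a fair reading of the intention, and the trial may well score RA correctly. It does not rescue the text: the article states a complete rule and no other section corrects it.

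The article also claims only that sensitivity variance is reduced, not that it is eliminated. A plain difference does neither for a multiplicative gain.

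Three stronger readings are tempting, and the documents do not support them.

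- *The treatment contrast would be biased.* Participants are randomised. If device sensitivity is unrelated to group, it adds noise and creates no difference between arms. Nothing in the article links devices to groups, or says that devices change between waves.
- *The supervised walk itself would be credited as a better rhythm because of this formula.* The normalised index also rises with M10. With M10 = 20000 and L5 = 2000, raising M10 to 22000 moves the difference from 18000 to 20000 and the index from 18000/22000 = 0.818 to 20000/24000 = 0.833. The movement is smaller but in the same direction, so this does not distinguish the two formulas.
- *M10 + L5 is the denominator the trial meant.* The article gives none. It is one suitable choice, to be checked against reference [108].

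**Conclusion.** The point stands as an internal contradiction in an outcome definition: the written formula is an absolute amplitude in device counts and cannot have the property claimed for it. This conclusion needs only the algebra of Step 1 and the premise that sensitivity acts multiplicatively.

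The size of the consequence rests on assumptions. If RA is scored literally, the expected harm is lost precision, from slight (variance up about 8.5% at a gain CV of 5%) to substantial (more than doubled at 20%). The documents do not show where in that range the devices lie.

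Severity is moderate. RA is one of three actigraphy variables among many outcomes. The sample size section rests on effects on cognition, so no power statement depends on RA. The recordings themselves are unaffected. A reader might infer that the trial deliberately chose an absolute measure; the name and rationale point instead to a drafting slip, and the article does not settle it.

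**What to change.** Replace the calculation sentence with the full formula, including a denominator that scales with the counts. A suitable form is RA = (M10 - L5)/(M10 + L5), with M10 and L5 the mean activity levels taken from the average 24-hour pattern; it runs from 0 to 1, higher meaning a larger relative contrast between day and night. Check it against reference [108] before fixing it, apply the same formula at baseline and all six follow-up waves, and confirm that the scoring code matches. If M10 - L5 is also of interest, report it separately under the name absolute amplitude, without the claim about sensitivity.

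The cost is one line of text and one line of scoring code. No new data are needed, and anything already scored as a difference can be rescored from the stored recordings.
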